**Methods:**

Eight hundred women will be recruited in early pregnancy from 4 clinical sites within Ireland, the UK, Spain, and Australia. Women will be screened for eligibility using the validated Monash GDM screening tool. Participants will be enrolled from 12 to 24 weeks’ gestation and randomised on a 1:1 basis into the intervention or control arm. Alongside usual care, the intervention involves mHealth coaching via a smartphone application, which uses a combination of synchronous and asynchronous video and text messaging, and allows for personalised support and goal setting with a trained health coach. The control arm receives usual care. All women and their children will be followed from early pregnancy until 12 months postpartum. The primary outcome will be a difference in maternal body mass index (BMI) of 0.8 kg/m^2^ at 12 months postpartum. Secondary maternal and infant outcomes include the development of GDM, gestational weight gain, pregnancy outcomes, improvements in diet, physical activity, sleep, and neonatal weight and infant growth patterns. The 5-year project is funded by the EU Commission Horizon 2020 and the Australian National Health and Medical Research Council. Ethical approval has been received.

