### Sample size

The study is an effectiveness trial and will use intention-to-treat analysis. Based on the primary outcome of maternal weight status at 12 months postpartum, to detect a 0.8-kg/m^2^ BMI difference between the groups with a standard deviation of 2 kg/m^2^ BMI, a type I error rate of 5%, and to achieve 80% power, 800 women need to be recruited to the trial (i.e. 400 in each arm of the study). This incorporates an assumed retention rate of 70% which is more conservative than previous studies to allow for country-level variance in retention. Each site will recruit 200 women over a 12-month period. Based on previous experience recruiting women from this setting and examining the potential numbers of eligible women using the current Monash Health rate of women scoring 3 or higher on the GDM screening tool (estimated to be approximately 33% prevalence), it is anticipated that recruitment will take around 12 months.

The study flow is described in Fig. 1.

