**Breastfeeding**	1. Iowa Infant Feeding Attitudes Scale (IIFAS) 2. Adapted version of the Australian National Infant Feeding Survey 2010 and InFANT Extend Study	1. The IIFAS has been validated in English and Spanish, with good reliability. 2. Adapted questions will be used from the Australian National Infant Feeding Survey and InFANT Extend Study to assess levels of breastfeeding, feeding styles (including combinations of breast milk and formula), experience of pumping, timing and frequency of feeding, and age of weaning. **Measurement units:** Continuous: IIFA score (17–85) Categorical: IIFAS scores will be categorised into groups: (1) positive to breastfeeding, (2) neutral, and (3) positive to formula feeding. Groups will be created based on previous breastfeeding experience, breastfeeding intentions, and meeting breastfeeding and infant feeding recommendations. **Analysis:** Compare the mean/median and SD/IQR and categories	- Pregnancy (12–24 weeks’ gestation) - Postpartum (3, 6, 9, 12^a^ months)	[34–37]
**Health status**	EuroQol-5 Dimension (EQ 5-D-L)	The EQ 5-D-L is a standardised instrument for measuring generic health status and has been extensively validated in over 200 countries. **Measurement units:** Continuous: self-rated EQ visual analogue scale (1–100), score 1–5 for five dimensions: mobility, self-care, usual activities, pain/discomfort, and anxiety/depression (score 1–5) Categorical: high/low across the five dimensions **Analysis:** Compare scores in categories, mean/median, and SD/IQR for visual analogue scale	- Pregnancy (12–24 weeks’ gestation) - Postpartum (12 months)^a^	[38, 39]
**Psychological health**	Edinburgh Postnatal Depression Scale (EPDS)	The EDPS is a questionnaire originally developed to assist in identifying possible symptoms of depression in the postpartum period. It also has adequate sensitivity and specificity to identify depressive symptoms in the antenatal period and is useful in identifying symptoms of anxiety. The EDPS has been extensively validated in multiple languages including Spanish, with good sensitivity, reliability and established validity against diagnostic interviews. **Measurement units:** Continuous: score (1–25) Categories: at-risk of depression (< 13, yes/no) **Analysis:** Compare the mean/median and SD/IQR and categories	- Pregnancy (12–24 weeks’ gestation) - Postpartum (3, 6, 9, 12^a^ months)	[40–42]

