### Postpartum assessments

It will be encouraged that weight will continue to be recorded weekly by participants using the digital scales provided. Breastfeeding will be assessed using an adapted version of the Australian National Infant Feeding Survey 2010 and InFANT Extend Study questionnaires to assess the history of breastfeeding, and for those that breastfed, their experience of feeding, pumping, and timing over the 3 monthly intervals (3, 6, 9, 12 months) [36, 37]. Psychological health will be assessed by the Edinburgh Postnatal Depression Scale (EPDS) and sleep quality by the Pittsburgh Sleep Quality Index (PSQI) at the same intervals [38, 43]. Parental-report infant weight (kg), length (cm), and head circumference (cm) will be collected at 3, 6, and 9 months. All metrics and questionnaires being completed postpartum are detailed in Table 1.

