Baseline characteristics will be compared between the intervention and control groups using the *χ*^2^ tests, the independent *t*-tests, and/or the Wilcoxon rank-sum test, as appropriate. Primary and secondary outcomes will be evaluated using repeated-measures analysis of variance (ANOVA) or mixed model analyses. Two-sided tests will be used, with a level of *P* < 0.05 determining statistical significance. Comparisons of the assessment times (the baseline and 12 months postpartum differences) within each treatment group (control or intervention) will be based on *t*-tests that utilise the standard errors of the differences that are computed as part of the repeated-measures analysis. Covariates included in the model will be kept to a minimum—site is the only covariate expected. The impact of loss to follow-up will be minimised by using a marginal model, which is not subject to list-wise deletion: each participant will contribute all time-specific measurements made to the model. Missing data will be reported for each outcome and handled by applying multiple imputation methods [60]. Subgroup analyses will be carried out to investigate the site differences based on the substantial demographic and operative differences in the four clinical sites. There are no interim analyses planned. Analyses will be conducted using the IBM SPSS software (version 26.0 or later; IBM), STATA version 12 or later (Stata Corp., College Station, TX, USA), or SAS software (SAS Institute Inc., Cary, NC, USA), as appropriate for analysis type. Data analysts will be blinded to group assignments.

A statistical analysis plan and data management plan have been prepared for the project which outlines plans for data entry, coding, confidentiality, security, and analysis in line with best practice (Additional file 2). Each clinical site is incorporated in this data management plan and provided the details to their relevant ethics committee. The project has an independent data manager who oversees the data monitoring and analyses and reports back to the RCT Working Group. There is no formal data monitoring committee; however, the external advisory board receives reports from the data manager.

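### Breastfeeding duration is right-censored at 12 months or at loss, but the analysis rule stated for all secondary outcomes (ANOVA or mixed model, with multiple imputation) does not handle censoring

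*Protocol article*

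**What the plan says.** The Outcome measurements section lists breastfeeding, both any and exclusive, and its duration among the secondary outcomes. Observation has a fixed end: "All women and their children will be followed from early pregnancy until 12 months postpartum" (Abstract, Methods). Feeding is asked about by questionnaire, covering "their experience of feeding, pumping, and timing over the 3 monthly intervals (3, 6, 9, 12 months" postpartum (Postpartum assessments). The Breastfeeding row of Table 1 adds "timing and frequency of feeding, and age of weaning" to what is collected.

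The Statistical analyses section sets the method without exceptions: "Primary and secondary outcomes will be evaluated using repeated-measures analysis of variance (ANOVA) or mixed model analyses". On incomplete data it says that loss to follow-up is limited by a marginal model in which "each participant will contribute all time-specific measurements made to the model", and then: "Missing data will be reported for each outcome and handled by applying multiple imputation methods". The Sample size section expects substantial loss: "This incorporates an assumed retention rate of 70" per cent.

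The article nowhere mentions censoring, Kaplan-Meier, log-rank, Cox or restricted mean methods.

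**The concern.** Duration is one number per woman, and for many women only a lower bound is known. A woman still feeding at 12 months has no stop date. A woman lost after reporting feeding at 6 months is known to have fed for at least 6 months and no more than that is known. Repeated-measures ANOVA and mixed models have no means of using such a bound. The marginal-model safeguard protects outcomes measured repeatedly, and duration has no repeats to contribute. Standard multiple imputation learns from women whose stop date was seen, who are the earlier stoppers. Unless imputed values are held above the last time the woman was known to be feeding, it tends to reproduce the distribution of short durations.

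The unobserved values are mainly the long ones, and the intervention supports breastfeeding. If coaching works, more stop dates will be missing in the intervention arm, and a method that ignores censoring will understate the effect. What is at stake is a missed or understated effect on this secondary outcome, not the trial's main conclusion.

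**Working it through.** The article gives no figure for breastfeeding duration, so there is no plan figure to reproduce. The calculation is an illustration.

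**Inputs from the article.** 400 women per arm; retention 70%, so loss 1 − 0.70 = 0.30; end of observation 12 months; questionnaires at 3, 6, 9 and 12 months; two-sided 5% level.

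**Assumptions, not in the article.** Exponential time to stopping; 35% of controls still feeding at 12 months (range 20–50%); hazard ratio for stopping 0.75; the 30% lost split equally over last contacts at 0, 3, 6 and 9 months (0.075 each), independent of feeding.

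**1. Rates.** Control λ₀ = −ln(0.35)/12 = 0.0875 per month; intervention λ₁ = 0.75 × 0.0875 = 0.0656. With S(c) = exp(−λc), S(12) is 0.350 and 0.455.

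**2. True difference in months fed within the first year.** R(12) = (1 − S(12))/λ. Control 0.650/0.0875 = 7.43; intervention 0.545/0.0656 = 8.31. Difference 0.88 months.

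**3. Women with no observed stop date.** 0.70·S(12) + 0.075·[S(0) + S(3) + S(6) + S(9)].
- Control: 0.245 + 0.075 × (1 + 0.769 + 0.592 + 0.455) = 0.456.
- Intervention: 0.319 + 0.075 × (1 + 0.821 + 0.675 + 0.554) = 0.547.

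About half of all women, and more in the intervention arm.

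**4. Observed stop dates only.** The mean is Σw[R(c) − c·S(c)] / Σw[1 − S(c)], where w is the share of women with last contact c.
- Control: 2.530/0.544 = 4.65.
- Intervention: 2.215/0.453 = 4.89.

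Difference 0.24 months.

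**5. Scored at last contact.** 0.70·R(12) + 0.075·[R(3) + R(6) + R(9)], with R(0) = 0.
- Control: 5.201 + 0.075 × 13.536 = 6.22.
- Intervention: 5.814 + 0.075 × 14.480 = 6.90.

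Difference 0.68 months. If women with no feeding questionnaire are treated as missing and not as zero, divide by 0.925: 0.74 months.

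**6. Censored analysis.** Observed stops: 400 × 0.544 + 400 × 0.453 ≈ 399. Schoenfeld power: Φ(√(399/4) × |ln 0.75| − 1.96) = Φ(2.87 − 1.96) = 82%.

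**7. Simulation for the remaining powers and for imputation.** Unbounded imputation here means normal draws from each arm's observed stop dates, 20 imputations. Ranges cover repeat runs.

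| Handling (35% of controls feeding at 12 months) | Difference (months) | Power |
|---|---|---|
| Missing stop dates dropped | 0.24–0.26 | 11–12% |
| Imputed with no lower bound | 0.25–0.26 | 11–13% |
| Scored at last contact | 0.67–0.70 | 57–60% |
| Same, women with no questionnaire missing | 0.73–0.74 | 67–68% |
| Capped at 12, women followed to 12 months only | 0.87–0.90 | 67–73% |
| Censored analysis | hazard ratio 0.75–0.76 | 81–84% |

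**8. Sensitivity.** With 20% and 50% of controls feeding at 12 months, steps 2, 4 and 5 give true differences of 1.00 and 0.70 months, 0.35 and 0.16 if dropped, and 0.79 and 0.54 at last contact. Step 6 gives 90% and 70% power. A separate set of assumptions (hazard ratio 0.80; 10%, 25% or 40% feeding at 12 months; 30% loss at a constant rate) gives the same ordering. Power is 29/13/8% if dropped, 70/55/40% at last contact and 79/70/59% for a log-rank type analysis.

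**The case against.** The strongest reply is that the article never says that women still feeding are dropped, scored at last contact or imputed below what is known. A reader might infer that the plan will discard the long durations. The text does not support that: it rejects list-wise deletion in the same paragraph, so the dropped-women row is a possible outcome and not a stated rule. This stands, and the sizes above are therefore conditional on the scoring chosen. The imputation row is closest to the words of the plan, but it too depends on an imputation model that is not described, and bounded imputation could work.

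A reader might also infer that capping at 12 months biases the comparison. It does not for months fed in the first year: among women followed to 12 months it targets the same quantity as a 12-month restricted mean, and under the assumed independent loss it recovers it. It understates only total duration, and it wastes the partial follow-up of women lost.

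Table 1's instruction, "Compare the mean/median and SD/IQR and categories", should not be read as a rule for duration. The only continuous unit in that row is the infant feeding attitudes score; the rest are categories.

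Finally, the methods sentence is a condensed default, and a separate analysis plan is said to exist. It may treat duration properly. But the article is not silent: it assigns a method family and a missing-data method to all secondary outcomes, and they do not suit this one. A mixed or marginal model of feeding status at each visit is legitimate, but it analyses status, not duration.

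**Conclusion.** The point holds in limited form. The stated rule for secondary outcomes does not accommodate a right-censored duration. Some ways of applying it would pull the arm difference towards zero: by nearly three quarters if missing stop dates are dropped or imputed without a bound (0.88 to about 0.25 months), and by about a fifth if women lost early are scored at last contact (0.88 to about 0.7). Capping at 12 months in women fully followed is essentially unbiased for the first year and costs only power, about 67–73% against about 82%.

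These sizes rest on an assumed share still feeding, an assumed hazard ratio, exponential stopping and loss unrelated to feeding, none of which the article gives. The direction was the same in every setting tried. One component of one secondary outcome is affected and the primary BMI comparison is not, so this is a minor correction.

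**What to change.** Exempt breastfeeding duration, any and exclusive separately, from the general ANOVA, mixed-model and imputation rule. Analyse it as time to stopping, censored at the last feeding questionnaire answered or at 12 months, and interval-censored where only the questionnaire interval is known. Report Kaplan-Meier curves with a site-adjusted Cox model, or the restricted mean to 12 months. Say how women with no feeding questionnaire are treated; they should not count as zero months. Feeding status at 3, 6, 9 and 12 months can stay in the mixed or marginal model as a separate analysis. If the unseen analysis plan already does this, a clause in the article's methods sentence pointing to it is enough.

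The cost is a few lines of analysis-plan wording. No new data are needed, since feeding is already asked about at all four postpartum time points, and the software packages named have survival routines.

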### Baseline assessments

Participants will attend the first study visit after recruitment in line with routine antenatal care. A researcher will facilitate participants in the intervention group with onboarding, including downloading the mHealth coaching app, account creation, and scheduling the initial coaching session. For participants in the control group, the research clinician will provide the women with a written leaflet with details of the approved website and show the woman how to access the health information on the Bump2Baby website. Demographic characteristics will be collected via questionnaire and will include maternal age, ethnicity, gravidity, parity, relationship status, educational attainment, employment status (of the participant and relevant partner), housing status, childcare responsibilities, and prior medical history.

Anthropometric measurements of maternal height (cm) and weight (kg) will be extracted from medical records, and all participants will also be provided with a set of digital scales (Smart Body Fat Scale, RENPHO©) for the duration of the study. Participants will be provided with a manual on how to use the scales appropriately and will be asked to weigh themselves approximately once a week. The scales will connect via Bluetooth, with an app on the participant’s phone, which facilitates automatic recording of this data when the individual is connected to a wireless network. Body mass index (BMI, kg/m^2^) will be calculated from these measurements. Blood pressure will also be measured using a calibrated blood pressure monitor at the baseline visit.

Participants will be asked to complete the online questionnaires, detailed in Table 1, within 1 week of the baseline visit before the first health coaching session for the intervention group.

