### 12-month postpartum assessment

At 12 months postpartum, participants will be contacted by the research team to arrange the last study visit. Participants will attend with their infant, and the following measurements will be collected: infant length (cm, assessed using a calibrated length mat), weight (kg), and head circumference (cm). Maternal height will be measured in centimetres and weight in kilograms. Standard operating procedures will be provided for these measurements. BMI *z*-score will be calculated using WHO growth standards [57].

Participants will be asked to complete further questionnaires, as detailed in Table 1, online the week before this appointment.

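### The plan does not fix how baseline BMI enters the primary model or which between-arm contrast is primary; adjusting for baseline is a nearly free gain in precision

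*Protocol article*

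**What the plan says.** All references are to the protocol article.

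- **Covariates** (Statistical analyses): "Covariates included in the model will be kept to a minimum—site is the only covariate expected".
- **Model** (same section): repeated-measures ANOVA or a mixed model, described further on as a marginal model to which each woman contributes every measurement she has. Baseline and 12 months are assessment times. The only contrast spelled out is the change from baseline to 12 months within each arm. No between-arm contrast is named, and nothing is said about equal baseline means.
- **Primary outcome**: the Abstract words it as a difference in BMI at 12 months postpartum. Outcome measurements words it as a reduction in the intervention group. Neither settles whether the arms are compared on level or on change.
- **Planning** (Sample size): "to detect a 0.8-kg/m^2^ BMI difference between the groups with a standard deviation of 2 kg/m^2^ BMI". The text does not say whether this SD is of 12-month BMI, of change, or a residual.
- **Measurement**: at baseline, "Anthropometric measurements of maternal height (cm) and weight (kg) will be extracted from medical records". At the final visit, "Maternal height will be measured in centimetres and weight in kilograms". No rule says which height is used for which BMI.

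**The concern.** A woman's BMI in pregnancy is likely to predict her BMI a year after birth, and it is already in hand. The plan names site as the only expected covariate and does not say how the baseline value is otherwise used, so two analyses with quite different precision both fit the text.

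- **Arm difference at 12 months.** In a model that leaves the baseline means free, with complete data, this is the raw difference in means. Baseline BMI then does nothing to reduce its variance.
- **Arm-by-time interaction.** This compares changes from baseline, so it uses the baseline value, though somewhat less efficiently than adjustment does.

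Adjusting for baseline, or fitting a common baseline mean, is at least as precise as either. What is at stake is the width of the primary confidence interval and, if between-woman spread is large, the power of the trial.

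**Working it through.** **Inputs from the documents.** Difference 0.8; SD 2; 400 per arm; retention 70%, so 400 × 0.70 = 280 completers per arm; two-sided 5% ("Two-sided tests will be used, with a level of *P* < 0.05 determining statistical significance").

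**Inputs assumed.** The correlation r between baseline and 12-month BMI, and any raw SD other than 2. The documents give neither, so a range is shown.

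**Step 1: the plan's own figure.** n per arm = 2 × (1.96 + 0.8416)² × 2² / 0.8² = 98.1, so 99. That is 198 evaluable and 198 / 0.70 = 283 recruited. The stated 800 is not reproduced. This is a separate matter. It bears on this point because 280 per arm is far more than SD 2 requires.

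**Step 2: formulas.** For raw SD s:
- SD with baseline adjustment = s × √(1 − r²)
- SD of change = s × √(2(1 − r))
- Standard error = SD × √(2/280) = SD × 0.0845
- 95% half-width = 1.96 × standard error = SD × 0.1656
- Power = Φ(0.8 / standard error − 1.96)

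**Step 3: power for 0.8 at 280 per arm.**

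| Assumed s | r | Adjusted SD | Change SD | Power, 12-month difference | Power, change | Power, adjusted |
|---|---|---|---|---|---|---|
| 5 | 0.5 | 4.33 | 5.00 | 47.3% | 47.3% | 58.9% |
| 5 | 0.7 | 3.57 | 3.87 | 47.3% | 68.6% | 75.5% |
| 5 | 0.8 | 3.00 | 3.16 | 47.3% | 84.9% | 88.4% |
| 5 | 0.9 | 2.18 | 2.24 | 47.3% | 98.8% | 99.1% |
| 4 | 0.8 | 2.40 | 2.53 | 65.8% | 96.3% | 97.6% |

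Half-widths at s = 5: 0.83 for the 12-month difference. At r = 0.8, 0.52 for change and 0.50 adjusted. At r = 0.9, 0.37 and 0.36.

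**Step 4: gain over a change analysis.** The ratio of variances is (1 − r²) / (2(1 − r)) = (1 + r)/2, which is 0.90 at r = 0.8 and 0.95 at r = 0.9. The saving is therefore 10% and 5% of the variance.

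**Step 5: at the protocol's SD of 2.** Unadjusted standard error = 2 × 0.0845 = 0.169, and 0.8 / 0.169 − 1.96 = 2.77, so power is 99.7%. If 2 is the raw SD, the half-width falls from 2 × 0.1656 = 0.33 to 0.20 at r = 0.8 (adjusted SD 1.20) or 0.14 at r = 0.9 (adjusted SD 0.87). If 2 is already a change or residual SD, baseline has been counted and the further gain is small.

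**Step 6: height.** An assumed error of 1 cm at BMI 30 and 165 cm moves one woman's BMI by about 30 × 2 × 1/165 = 0.36, and 2 cm by 0.73. Treated as an independent error SD added to a change SD of 2.24, this gives √(2.24² + 0.36²) = 2.27 or √(2.24² + 0.73²) = 2.36, an interval 1% to 5% wider.

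**The case against.** **Baseline BMI is already in the model.** A reader might infer from the covariate sentence that it is ignored. The text does not support that. Baseline is an assessment time, and a variable analysed as a repeated outcome would not also be listed as a covariate. If the effect is the arm-by-time contrast, most of the gain is already captured at high r. This stands, and it is why 47% cannot be quoted as the trial's power. What remains is that the text does not choose this contrast and does not impose a common baseline mean.

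**The SD of 5 is not in the documents.** This also stands. One might argue that an SD of 2 makes sense only for a baseline-adjusted quantity, so that planning and model disagree. The documents do not say so. They leave the type of SD undefined, and a change SD of 2.24 (SD 5, r = 0.9) lies close to 2, so a change analysis would fit.

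**Omitted covariates do not bias a randomised comparison.** Correct. Chance imbalance is already reflected in the standard error. The planned tests of baseline balance are not said to drive adjustment.

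**Gestational age and height.** Nothing shows that gestational age at the baseline weight explains much of 12-month BMI. It is recorded at scan, where available, and is not in the list of baseline characteristics. A height error in one woman is not comparable with 0.8 between arm means, because it averages out over about 280 per arm and nothing suggests that it differs by arm.

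**A statistical analysis plan exists and is not shown.** It may name the contrast and the baseline constraint, and their absence from an article would not by itself be a fault. But the article does make a positive statement on covariates, and "Covariates included in the model will be kept to a minimum—site is the only covariate expected" points away from baseline adjustment, even allowing for its soft wording.

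**Conclusion.** The point holds as a matter of precision and of a contrast left open. The stated model is not invalid, and the trial is not shown to be underpowered. The size depends on two things that the documents do not give.

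- **Which contrast is primary.** If it is the unconstrained 12-month difference, the loss is large under an assumed raw SD of 5: 47% power against 88% (r = 0.8) or 99% (r = 0.9). If it is the arm-by-time change, the loss at those correlations is small: 84.9% against 88.4%, and 98.8% against 99.1%. At a lower correlation the change analysis loses more, for example 68.6% against 75.5% at r = 0.7.
- **What the SD of 2 describes.** If the analysed quantity has SD 2, power at 280 per arm is 99.7% without adjustment, and the benefit is only a narrower interval.

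Baseline adjustment or a common baseline mean does at least as well under every reading. The change is worth making whichever assumption turns out to be true.

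**What to change.** Replace the covariate sentence in Statistical analyses with:

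> The primary analysis is the between-arm difference in BMI at 12 months, from a model with arm, site and baseline BMI (ANCOVA, or a longitudinal model with a common baseline mean).

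The longitudinal form suits the plan's wish to use every measurement, since a woman with only one of the two values still contributes. Apply the same rule to secondary outcomes that have a baseline value. If the unseen analysis plan already says this, bring the protocol sentence into line with it.

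Two minor additions:
- Use one height per woman for both BMIs, which removes a small source of noise.
- Gestational age at the baseline weight is an optional covariate, where it can be derived from scan or due-date records.

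The fix should not require a weight taken before allocation. Randomisation precedes the first antenatal visit, and the documents do not show that every woman has such a weight. It is enough to define which recorded weight is the baseline one.

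The cost is wording, settled before the data are unblinded. Baseline BMI and site need no new data collection.
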